#### Smoking behaviour assessment

To obtain data about smoking behaviour, a short questionnaire regarding smoking from a national health questionnaire used by the federal government was selected[20]. This questionnaire includes questions for smokers as well as for former smokers.

#### Quality of life assessment

The Dutch translation of the Short Form 36 (SF-36) will be used to measure Health Related Quality of Life (HRQoL). This version was successfully tested in a Belgian and Dutch population with a Chronbach's alpha coefficient ranging from 0.81 to 0.91[21,22].

#### Assessment of psychological variables

##### Stages of change

Stages of change is a construct from the TransTheoretical Model[23]. The stages of change were assessed using a single table for assessing physical activity, diet and quitting smoking (Table 2). The formulation of the statements was based on the remarks about standardization in a recent meta-analysis[24] and questionnaires for measuring stages of change for physical activity[25] and fat intake[18].

**Table 2 T2:** Assessment of stages of change

	30 minutes of moderate PA daily or 3*/week intensive PA	Low fat diet and 5 portions fruit and vegetables daily	Not smoking (if relevant)
I'm not performing the behaviour and I do not intend to in the next 6 months			
I'm not performing the behaviour but I plan to in the next 6 months			
I'm not performing the behaviour but I plan to in the next 30 days			
I perform the behaviour but no longer than 6 months			
I perform the behaviour but already longer than 6 months			

##### Attitudes towards behaviour change

Attitudes are an important element in the Theory of Planned Behaviour[26]. As recommended by Ajzen and Fishbein[27], a measure of attitude towards the target behaviour was obtained using 3 evaluative semantic differential scales. Study participants are asked to assign a value along a 7-point scale between opposing evaluative adjectives (e.g. pleasant-unpleasant, good-bad, relaxing-stressing)[28]. An example of an item requesting a value assignment for "To eat low fat every day for me is" along a 7-point scale between the opposing evaluative adjectives "pleasant" and "unpleasant".

##### Self-identity towards behaviour change

Self-identity is seen as the extent to which people see them fulfilling different societal roles[28]. In this study it is seen as the way people define themselves regarding a specific health behaviour (physical activity, a healthy diet and quitting to smoke). The question list includes 2 items for self-identity for each type of health behaviour. An item for physical activity is, for example, "I think of myself as someone who is physically active". An item for diet is, for example, "I am someone who often thinks about the importance of a healthy diet for my health". For smoking, an item for self-identity is, for example, "I am someone who thinks quitting to smoke is important". All were measured on 7-point Likert scales, anchored by strongly disagree-strongly agree.

##### Perceived control over behaviour

Perceived control over behaviour is related to self-efficacy, the two variables are significantly and highly correlated [29]. However, if the two variables are entered into a regression model for behavioural intention, they contribute independently to the model. Perceived behavioural control is usually measured in terms of difficulty or ease of performing the behaviour. This means that behaviours that are not under individuals' full volitional control are included [29]. Perceived control over behaviour is measured with 1 item. Participants indicate the extent to which they agreed with each item on 7-point Likert scales from strongly disagree-strongly agree. The items include "I have the feeling that daily 30 min moderate PA or 3 times sports a week is completely in my control the next month", and " I have the feeling that quitting to smoke is completely in my control the next month". The selection of these items was based on prior research with this concept regarding health-related food choice[28].

##### Self-efficacy

Self-efficacy is usually measured in terms of individuals' confidence in their ability to perform the behaviour [29]. Self-efficacy is measured with 2 items for each type of health behaviour. Participants rated these items using a 7-point Likert scale, anchored by strongly disagree-strongly agree. The items include "I am capable to adopt daily PA for 30 minutes or sport 3 times a week in the next month, also on days I feel bad, tired, stressed or depressed", "I think I am capable to adopt a low fat diet in the next month, also on days that I am very busy or family and friends request extra time from me" and "I am capable to quit smoking the next month, also on days I feel bad, tired, stressed or depressed". The items for self-efficacy were based on prior research with this concept regarding health-related food choice[28].

##### Autonomous motivation for behaviour change

People are autonomously motivated if they experience a true sense of volition and choice and act because of the personal importance of the behaviour [30,31]. If people are autonomously motivated the behaviour they perform is said to be autonomously regulated. Autonomous regulation is assessed with the Treatment Self-Regulation Questionnaire [31]. The Treatment Self-Regulation Questionnaire was used in former research on the effect of an intervention on diet and smoking cessation [31]. For assessing autonomous motivation for physical activity the Behavioural Regulation Exercise Questionnaire II (BREQ-II) was chosen for the measurement of autonomous motivation, with good psychometric properties[32,33].

##### Intention towards behaviour change

Intention to engage in a behaviour is a direct precursor to engaging in the behaviour itself [29]. Behavioural intention was assessed using 3 items: "I plan to adopt a healthy diet (low on fats and 5 portions of fruit or vegetables) in the next month", "I plan to adopt daily PA or 3 times sport a week in the next month" and "I plan to quit smoking in the next month". The 3 items could be answered using a 7-point Likert scale, with endpoints labelled strongly disagree-strongly agree. These items were based on previous research [30].

##### Social support

Social support is an important variable influencing behaviour change[34]. Consequently, several items were included in the question list to measure the amount and nature of experienced social support of the study participants. The answer possibility involved a 3-point Likert scale with following options: never/almost never, sometimes and often. The items included how often people feel encouraged by partner support, support of children older than 12, support of family or friends, support of colleagues, support by GP and support by the PreCardio-team for adopting a healthier diet, being more physically active and quitting smoking. Furthermore, study participants are asked if they have a fixed sports partner with answer possibilities: yes, sometimes and no.

#### Assessment of physical fitness

A step test will be used for assessment of physical fitness. The step test procedure used was modified from earlier procedures[35]. The step test consisted of stepping up and down a platform at a constant controlled by a metronome (90 beats per minute). Each beat initiates the movement of one leg up or down the platform. The stepping period lasted for 5 minutes. The height of the platform was determined according to patients' height and risk for complications (e.g. former personal ischemic event). For individuals smaller than 160 cm or with a former event a platform of 25 cm was used. For individuals with a height between 160 and 180 a platform of 33 cm was used. For people with a height above 180 cm a platform of 40 cm was used. The heart rate frequency was recorded between 1 minute and 1:30 minutes after completing the step test or stop because of exhaustion) in sitting position, between 2 minutes and 2:30 and between 3 minutes and 3:30. With a formula, the physical fitness level of the patient can be calculated. Few materials are needed in order to execute this test: a platform with a specific height, a stopwatch, and a metronome in order to determine the stepping speed.

### Interventions

#### Minimal intervention

##### Medical prevention consultation

The interventions targeted on medical parameters include a first medical prevention consultation with the GP. In this medical prevention consultation the cardiovascular risk (risk on having a heart attack in the next 10 years) will be calculated using a new computer programme. This computer programme is called "Electronic Prevention Record" (EPR). Innovative about the EPR is its connection to "Electronic Medical Record" (EMR). The EMR is also a computer programme, a record about the medical history and treatment provided to the patient. In the province of Limburg, the setting for the PreCardio-study, 75% of the GPs use an EMR[36]. In Belgium, 70% of the GPs use an EMR [37]. In Belgium there are 17 different providers of EMRs. The EPR generates, after a limited input (thanks to the connection to the EMR), the cardiovascular risk, the therapeutic goals (targeted on medical parameters and behaviour change) and a target date for the next follow-up consultation. This date is dependent on the determined cardiovascular risk. During these medical prevention consultations medical practice will be performed: measurement (e.g. blood pressure) and installation of treatment to influence medical parameters. Supplementary, the GP performs stage of change assessment (Table 2) using the EPR. The GP asks for PA and diet which statement fits the participant's situation best. If it is a smoker, the stage of change for quitting smoking is assessed as well. The stage of change assessment is for the control group not followed by tailored feedback for behaviour change.

All data collected at the medical prevention consultation are stored in the EPR that is connected to the EMR (Fig 4). Therapeutic goals in line with cardiovascular risk are determined. These goals, together with the data provided by the study participant are electronically sent to the study office by a secured connection. The information from the intervention group is closely examined and the participants of the intervention group will receive a reminder from the study office when it is time to plan their next medical prevention consultation.

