#### Primary aims

1. To examine the effects of medical and behavioural interventions on medical parameters such as systolic blood pressure, diastolic blood pressure, total blood cholesterol level, blood glucose level (HbA1c), overweight and obesity, BMI.

2. To examine the effects of medical and behavioural interventions on health related behaviour such as physical activity; fat; fruit and vegetable intake; and smoking behaviour.

3. To examine the effects of medical and behavioural interventions on overall cardiovascular risk mediated by changes in medical and/or behavioural risk factors.

4. To determine the proportion study participants with a 10% reduction in systolic blood pressure with participants with hypertension

5. To determine the proportion study participants with a 10% reduction in diastolic blood pressure with participants with hypertension

6. To determine the proportion study participants with a 10% reduction in total cholesterol with patients with hypercholesterol

7. To determine the proportion study participants with a 10% reduction in HB1Ac with initial HB1Ac >7% (high risk)?

8. To determine the proportion study participants with a 10% reduction in weight with initial BMI >25 kg/m^2^?

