### Design

The intervention group as well as the control group receive a first medical prevention consultation with a GP of their choice. Fig 1 represents the study design. The GP performs a cardiovascular risk assessment using an adapted risk assessment flowchart (Fig 2). Medical data such as systolic and diastolic blood pressure, total blood cholesterol, LDL cholesterol (and HbA1c) are collected at this medical prevention consultation prior to risk determination. The intervention and the control group receive the therapeutic goals from the risk assessment flowchart. The intervention group receives supplementary tailored feedback regarding behaviour change based on the TransTheoretical Model or the Stages of Change Model[23]. Thus, the feedback is tailored to the stage of change the study participants are in for physical activity, diet and quit smoking. After the first medical prevention consultation all study participants get access to a website which includes a question list for baseline data collection. The intervention group receives tailored advice on this question list. The control group receives general advice to impede or avoid drop-out but with caution for causing bias. The question list includes items for physical activity assessment, fat intake assessment, fruit and vegetable intake assessment, smoking behaviour assessment and assessment of psychological variables. The physical fitness will be determined at the GP's office, at study participants home and at baseline data collection during the large event. For follow-up data collection these assessments will take place regularly. The intervention group receives the maximal intervention and the control group receives the minimal intervention.

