### Study measurements

The study measurements in the PreCardio-study include cardiovascular risk assessment. Supplementary a questionnaire assessing physical activity; fat, fruit and vegetable intake; smoking behaviour and psychological variables will be filled out. Furthermore, physical fitness assessment will be performed. These assessments will take place at certain times during the 3 year follow up of the study (Table 1).

**Table 1 T1:** Data collection

**Assessment of**	**Instrument**	**Means**	**0 m**	**4 m**	**6 m**	**8 m**	**12 m**	**18 m**	**24 m**	**30 m**	**36 m**
Cardiovascular risk (BMI, blood pressure, cholesterol, HBA1c)	Risk Calculator	GP	YES	~RISK	NO	~RISK	YES	NO	YES	NO	YES
Physical Activity (PA)	IPAQ	Website	YES	NO	YES	NO	YES	YES	YES	YES	YES
Fat intake	Questionnaire	Website	YES	NO	YES	NO	YES	YES	YES	YES	YES
Fruit & Vegetable intake	Food Frequency Questionnaire	Website	YES	NO	YES	NO	YES	YES	YES	YES	YES
Smoking behaviour	Questionnaire	Website	YES	NO	YES	NO	YES	YES	YES	YES	YES
HRQol	SF-36	Website	YES	NO	YES	NO	YES	YES	YES	YES	YES
Stages of change	Questionnaire	Website	YES	NO	YES	NO	YES	YES	YES	YES	YES
Attitudes	12 items	Website	YES	NO	YES	NO	YES	YES	YES	YES	YES
Self-identity	6 items	Website	YES	NO	YES	NO	YES	YES	YES	YES	YES
Perceived control over behaviour	3 items	Website	YES	NO	YES	NO	YES	YES	YES	YES	YES
Self-efficacy	6 items	Website	YES	NO	YES	NO	YES	YES	YES	YES	YES
Social Support	15 items	Website	YES	NO	YES	NO	YES	YES	YES	YES	YES
Physical fitness	Step test	Event/GP/home	YES	NO	NO	NO	YES	NO	YES	NO	YES

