##### Website with minimal information

The website available for the control group is limited and contains information about the minimal intervention (i.e. medical prevention consults *without *tailored feedback and *without *reminder from study office). It is also used as a means for study measurements at certain times during the 3-year follow up (Table 1). This limited website contains *general *feedback after the questionnaire with multiple assessments has been filled out by the study participants from the control group. This *general *feedback (= not tailored) is about physical activity, fat intake and smoking and is modified for different measurements in time to avoid drop-out. However, the advice will always be formulated very abstract to avoid 'contamination' of the control group as was the case in another multiple risk factor cardiovascular intervention study[38].

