Secondly, the intervention group receives the supplementary service of being reminded of their next follow-up prevention consult by the study office. As mentioned above, this target date is dependent on the cardiovascular risk of the participant. This reminder will be send by mail or the patient will be reminded by telephone.

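### The medical primary outcomes come only from GP prevention consultations, for which only the intervention arm is reminded, and no arm-neutral prompt for the 12, 24 and 36 month measurements is described

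*Protocol article*

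**What the plan says.** All places are in the protocol article.

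- **Primary aims.** The first aim concerns "medical parameters such as systolic blood pressure, diastolic blood pressure, total blood cholesterol level, blood glucose level (HbA1c), overweight and obesity, BMI". Aim 3 is overall cardiovascular risk, and aims 4 to 8 are responder proportions on blood pressure, cholesterol, HbA1c and weight.
- **Design.** The medical data "are collected at this medical prevention consultation prior to risk determination".
- **Study measurements, Table 1.** The row that begins "Cardiovascular risk (BMI, blood pressure, cholesterol, HBA1c" names the GP as the only means of collection, at 0, 12, 24 and 36 months for everyone, with 4 and 8 months depending on risk. No other visit for these outcomes is described.
- **Minimal intervention, Medical prevention consultation.** The GP's software generates a risk-dependent target date for the next consultation in both arms. The section then says: "The information from the intervention group is closely examined and the participants of the intervention group will receive a reminder from the study office".
- **Maximal intervention.** The reminder is listed as the second extra service: "the intervention group receives the supplementary service of being reminded of their next follow-up prevention consult by the study office". On its form: "This reminder will be send by mail or the patient will be reminded by telephone".
- **Website with minimal information.** The control package is described as "medical prevention consults *without *tailored feedback and *without *reminder from study office".

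**The concern.** One consultation does two jobs. It delivers part of the programme, and it is the only stated source of the medical primary outcomes. The prompt to attend is a study-office service given to one arm and expressly withheld from the other. If the reminder works, it raises attendance, and attendance here is also what produces an outcome value. A successful intervention component can thus become differential missingness.

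Control participants who come without a reminder may be more health-conscious than the rest of their arm, or may have worse values and closer GP contact. In the first case the observed control mean is too favourable and a real benefit is masked. In the second it is too unfavourable and the benefit is inflated. Timing may also drift apart, because prompted participants are more likely to be measured near the scheduled month. The regression on change in overall risk to 3 years, announced under Analysis and power, depends on the 36-month GP value, and a value not recorded then cannot be recovered later.

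**Working it through.** **1. Inputs from the article.** Total 350, allocated 2:1 (Study population; Randomization), so about 233 and 117. Systolic pressure: difference 5 mmHg, SD 14 mmHg, two-sided 0.05, 200 and 100 analysed, stated power 82% (Analysis and power).

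**2. The plan's own figure.** The standard error is 14 × √(1/200 + 1/100) = 1.715 mmHg and the noncentrality is 5/1.715 = 2.916. The noncentral t distribution with 298 degrees of freedom gives power 0.828, which agrees with the stated 82%. The sample size calculation is not in dispute.

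**3. Assumed attendance.** The article gives no attendance rates, so everything from here on is illustration. Suppose 85% of the intervention arm has a 36-month GP measurement: 0.85 × 233.3 = 198.

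| Control attendance | Analysed | Standard error | Power for 5 mmHg |
|---|---|---|---|
| 85% (equal) | 198 : 99 | 1.723 | 0.824 |
| 70% | 198 : 82 | 1.839 | 0.773 |
| 60% | 198 : 70 | 1.947 | 0.725 |

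**4. Bias among completers.** Let attendance follow a latent normal propensity that correlates ρ with systolic pressure. With attendance proportion p, the mean of attenders moves from the arm's true mean by ρ × 14 × φ(z_p)/p, where z_p is the p-quantile and φ the density of the standard normal. The ratio φ(z_p)/p is 0.274 at p = 0.85, 0.497 at 0.70 and 0.644 at 0.60. The bias in the between-arm difference is the control shift minus the intervention shift:

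| ρ | 85% vs 70% | 85% vs 60% |
|---|---|---|
| 0.1 | 0.31 mmHg | 0.52 mmHg |
| 0.2 | 0.62 mmHg | 1.03 mmHg |
| 0.3 | 0.93 mmHg | 1.55 mmHg |

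For example, at ρ = 0.3: 0.3 × 14 × (0.644 − 0.274) = 1.55 mmHg. As a share of the 5 mmHg target, the table runs from 6% (0.31/5) to 31% (1.55/5). The sign reverses with the sign of ρ.

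**5. A second, simpler model.** If attenders and non-attenders differ by D mmHg in both arms, the bias is the difference in attendance times D. With 90% attendance in the intervention arm and 80, 70 or 60% in the control arm, D = 5 gives 0.5, 1.0 or 1.5 mmHg. Over D = 3 to 7 the range is 0.3 mmHg (0.10 × 3) to 2.1 mmHg (0.30 × 7). The order of magnitude is the same.

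**6. What the models leave out.** Both work on the unadjusted cross-sectional value. If selection acts mainly through baseline health, a baseline-adjusted or change-from-baseline analysis removes part of it. The t-test described in the article compares means; the regression on overall risk uses change from baseline.

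**The case against.** The strongest reply is that the article speaks of two different things. The reminder concerns the next follow-up consultation, whose date depends on calculated risk. The 12, 24 and 36 month measurements are fixed calendar points, the same for both arms in Table 1. How participants are called to those measurements is not stated for either arm, and a condensed article may leave such logistics to the full protocol. This stands in part: it can be said only that no arm-neutral prompt is described, not that none exists. It does not dispose of the point, because the article affirmatively places control consultations outside the reminder service and names no other source for the medical outcomes.

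It is also fair that the reminder is a deliberate part of the maximal intervention. The treatment difference itself is no error. The weakness is that outcome collection is not separated from it.

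Some stronger readings are tempting, and the text does not support them:

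- *That control participants must remember for themselves for three years.* The GP's software sets a target date in both arms, and the control website varies its feedback over time to limit drop-out. Neither equals a reminder, but the control arm is not without any cue.
- *That incoming data are checked in one arm only.* The clause on close examination names the intervention group and is silent on control. It shares a sentence with the reminder and may only describe how reminders are triggered. Transfer of data to the study office is described under the consultation common to both arms.
- *That the smaller arm will lose the most data.* This depends on attendance rates that the documents do not give.
- *That the website questionnaires and the step test are affected as well.* No unequal prompting is described for either.

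Missing-data methods could be offered as the remedy, and the analysis plan is not shown. They would rest on untestable assumptions about participants who did not return, so equal prompting at source is the better protection.

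**Conclusion.** The point holds as a design weakness confined to the medical primary outcomes. As described, the consultation that yields them is prompted by the study office in one arm and expressly not in the other, with no neutral measurement prompt to offset this. Completeness and timing may differ by arm, and the direction of any bias cannot be known in advance.

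The size is illustrative. With 85% against 60–70% attendance at 36 months, power is about 73–77% instead of about 82% at equal 85% attendance. The unadjusted completer bias is about 0.3–1.6 mmHg if attendance correlates 0.1–0.3 with systolic pressure at SD 14, and smaller after baseline adjustment. If attendance turned out equal, the loss of power would vanish and, under these models, so would the bias. No figure in the article is wrong. The point should be fixed, but it does not by itself invalidate the trial.

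**What to change.** Separate measurement from intervention for the medical outcomes. For the 12, 24 and 36 month GP measurements, send every participant in both arms the same neutral study-measurement invitation, with the same wording, timing and number of contacts. Keep the reminders for risk-dated consultations as the intervention-only service. State this in the two sections on the medical prevention consultation (minimal and maximal intervention) and in the description of the control website, so that the control arm's lack of a reminder clearly refers to the risk-dated consultations only. If the full protocol already provides such an invitation, saying so is enough.

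The cost is one invitation per participant per annual wave: up to about 350, or about 117 additional ones (350/3) if the invitation replaces a contact that the intervention arm already receives. The downside is that somewhat more control participants may attend the annual consultation, which slightly narrows the contrast between the arms.
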